### 0.5 Method of intervention

Intervention group: CBT, 30 minutes per session, once a week for a total of 4 treatment sessions. If the patient is on medical treatment, it will be given in conjunction with medical treatment. Online intervention using a web conferencing application will be

66 provided for those who wish to use.  
67 Control group: No additional treatment during the study period. If on medical treatment,  
68 participants will continue the baseline medical treatment only. CBT will be provided at  
69 the end of the study. If desired, CBT will be conducted online using a web conferencing  
70 application.

71

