199 intervention. Based on the results of the pilot study, we concluded that it was

200 worthwhile to evaluate the efficacy of CBT for OAB and decided to design this study.

201

202 2. Purpose

203 The purpose of this study is to establish CBT for OAB based on conventional  
 204 behavioral therapies and to evaluate its efficacy in women with moderate to severe  
 205 OAB in a randomized controlled trial.  
 206

207 3. Study design  
 208 Open-label, parallel-group, multicenter, 1:1 randomized controlled trial  
 209

210 4. Selection of participants  
 211 4.1. Institutions  
 212 Department of Urology, Kyoto University Hospital  
 213 Department of Urology, Kyoto City Hospital  
 214 Department of Urology, Asukai Hospital, Kyoto Civil Medical Federation Ichioka  
 215 Urology Clinic  
 216

217 4.2 Inclusion and exclusion criteria  
 218 Inclusion criteria:  
 219 (1) Women between 20-80-year-old;  
 220 (2) Participants not having undergone any OAB treatment for more than 6 weeks or  
 221 participants taking pharmacotherapy lasting more than 6 weeks for OAB;  
 222 (3) Participants diagnosed with OAB based on their OAB symptom score (OABSS)\* (a  
 223 total OABSS score  $\geq 3$ , with an urgency score  $\geq 2$ ), with the total score being higher than  
 224 6 (OABSS; 6 to 11 points indicate moderate severity, 12 to 15 points indicate moderate  
 225 severity) (1);  
 226 (4) An Eastern Cooperative Oncology Group (ECOG) Performance Status of Grade 0;  
 227 and  
 228 (5) Participants who are able to understand explanations and sign a written informed  
 229 consent.  
 230

231 \*Overactive Bladder Symptom Score (OABSS):  
 232 It is a symptom score for OAB developed in Japan and used worldwide for diagnosis  
 233 and severity assessment (1). A urinary urgency score (Question 3) of 2 or higher and a  
 234 total score of 3 or higher are considered a diagnosis of OAB. Regarding severity, a total  
 235 score of 5 or less is considered mild, a score of 6-11 moderate, and a score of 12 or  
 236 more severe.  
 237

238 Exclusion criteria

- 239 (1) Abnormalities around the bladder (e.g., bladder cancer, bladder calculus, interstitial  
240 cystitis, endometriosis);  
241 (2) Urinary tract infection;  
242 (3) Surgery for urinary incontinence;  
243 (4) Pregnancy;  
244 (5) Disability to understand Japanese;  
245 (6) Depression;  
246 (7) Dementia; and  
247 (8) Participants judged otherwise unsuitable for participation by the researchers.  
248

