##### 274 (3) Lifestyle modifications

275 Identify lifestyle habits that may be risk factors for OAB (excessive water intake,  
 276 caffeine consumption, alcohol consumption) and establish strategies to improve them.

277 (4) Pelvic floor muscle training

278 Weak pelvic floor muscles are considered one of the causes of OAB. In conjunction  
 279 with proper posture and breathing techniques, increase pelvic floor muscle strength  
 280 through repeated awareness and contraction/relaxation exercises.

281 (5) Exposure

282 While the urge to urinate can be avoided by emptying the bladder frequently, the act of  
 283 frequent urination actually promotes the urge to urinate, leading to a vicious cycle.

284 Exposure (endurance) to the uncomfortable situation (urge to urinate) is encouraged to  
 285 increase tolerance to the urge (to extend the interval between urinations). A step-by-step  
 286 schedule should be planned, and the urination interval should be gradually increased by  
 287 consistently following the schedule.

288 (6) Relapse prevention

289 Review the series of sessions and compare the condition before and after treatment. List  
 290 the positive and negative aspects and help the participants solve problems independently,  
 291 such as how to continue the treatment in the future or what to do in case of symptom  
 292 exacerbation.

293       Using these six techniques, interventions that may be effective for OAB are  
 294 selected, and the therapist and the research participant collaborate to set treatment goals  
 295 and assign homework for each session. Each session consists of 30 minutes and  
 296 includes (1) introduction, (2) agenda, and (3) summary. The overall treatment will  
 297 comprise of (1) an introduction phase (1 session), (2) a practice phase (2 sessions), and  
 298 (3) a relapse prevention phase (1 session), totaling 4 sessions. As a basic rule,  
 299 interventions will be conducted every week, but a maximum interval of three weeks will  
 300 be allowed (an interval of more than three weeks will be considered a deviation from  
 301 the intervention). If the patient is already on oral therapy, the CBT should be  
 302 coordinated with the oral therapy.

303 Due to concerns about the risk of novel coronavirus transmission, the intervention will  
 304 be conducted online using a web conferencing application for those who wish to  

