| 4        | Review session 3 and homework
Relapse prevention
Plan the future's goal and encourage to continue the techniques
Total review                                                                                                                                                                             |

313

314

315 5.2. Therapist

316 The treatment therapist in this study shall be qualified as a specialists and supervisors  
 317 certified by the Japanese Urological Association, with a minimum of 10 years of clinical  
 318 experience. Additionally, participation in the CBT workshop, a training program  
 319 conducted by the Ministry of Health, Labor, and Welfare, is mandatory.

320

321 5.3 Assurance of Quality of Intervention

322 To ensure the quality of interventions, a review committee comprising urologists,  
 323 obstetricians/gynecologists, psychiatrists, clinical psychologists, and physical therapists  
 324 was established, and a treatment manual was developed. The therapist will conduct  
 325 interventions in accordance with this manual. A checklist is prepared for each session to  
 326 verify the achievement of each item.

327

328 5.4. Treatment of the control group  
329 CBT will not be administered during the study period. If the patient is receiving a drug  
330 treatment, only the baseline treatment will be continued. CBT will be provided after the  
331 completion of the study. Online CBT using a web conferencing application will be  
332 conducted for those who wish to participate.  
333

334 6. Data collection  
335 6.1 Baseline characteristics  
336 Age, height, weight, medical history, childbearing experience, menopause, highest  
337 education level completed, marital status, occupational history, and history of dysuria  
338 treatment will be assessed using a questionnaire at baseline.  
339

340 6.2. Outcomes  
341 Primary outcome:  
342 - Overactive Bladder Questionnaire (OAB-q) HRQoL total score (2)  
343 This is a QOL self-reported questionnaire specific to OAB. It consists of questions  
344 regarding the degree of distress and QOL due to symptoms. Week 13 (end of follow-up)  
345 is the primary assessment point. The HRQoL total score of the OAB-q is calculated on a  
346 100-point scale as follows: Minimum Clinical Important Difference (MCID) is 10  
347 points (20).  
348  $[150 - (\text{Question Score } 9+10+11+12+13+14+15+16+17+18+19+20+$   

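### Deviation 9.1(3) and PPS criterion 11.2(3) count added OAB treatment only when another hospital gives it, so the per-protocol set does not remove a drug added at the study site

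*Protocol*

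**What the plan says.** **Entry.** Inclusion criterion (2) in section 4.2 asks both arms for a settled regimen: no OAB treatment for more than 6 weeks, or "participants taking pharmacotherapy lasting more than 6 weeks for OAB".

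**Controls.** Section 0.5 states "Control group: No additional treatment during the study period" and, for those on medication, "participants will continue the baseline medical treatment only". Section 5.4 repeats the second part: "treatment, only the baseline treatment will be continued".

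**CBT arm.** Section 0.5 says "If the patient is on medical treatment, it will be given in conjunction with medical treatment". The sentence in section 5.1 that begins "If the patient is already on oral therapy, the CBT should be" goes on to ask for coordination with that therapy. Neither says whether an OAB drug may be started, switched or stopped.

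**Deviations and PPS.** Item (3) of section 9.1 makes additional OAB treatment a deviation if another hospital gave it. Criterion (3) of section 11.2 uses the same limit for membership of the PPS. Section 11.2 introduces the PPS as the patients who adhere to the protocol and then defines it by four criteria. Section 11.3.4 makes ITT the main analysis and the PPS a sensitivity analysis.

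**Setting.** The sites in section 4.1 are urology services, for example "Department of Urology, Kyoto University Hospital". Under section 5.2 the therapist is a specialist "certified by the Japanese Urological Association, with a minimum of 10 years of clinical" experience. Change in medication, including addition, is a secondary outcome (sections 0.6 and 6.2).

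**The concern.** A per-protocol criterion on added OAB treatment exists to show whether the result survives once participants with extra active treatment are set aside. Here the criterion depends on where the treatment was given rather than on whether it was given. The location it leaves out is the urology service the participant attends for the trial, which is an obvious place for a drug to be added. Agreement between the PPS and ITT results would then say nothing about co-treatment started on site.

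The second issue is symmetry. The same event, a drug added at the study site, breaches a rule in one arm and no stated rule in the other. Depending on how section 11.2 is read, it could lead to exclusion in one arm and retention in the other.

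**Working it through.** This is a check of wording. The protocol's sample size is not in dispute and serves only as a frame for scale.

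**Step 1. Does another listed item cover an on-site addition?**
- Section 9.1: (1) no intervention received; (2) interval over 3 weeks; (3) added OAB treatment at another hospital; (4) no valid data after the start of treatment. Only (3) concerns co-treatment, and it excludes the study site.
- Section 11.2: (1) all intervention sessions received; (2) interval under 3 weeks; (3) no added OAB treatment at other hospitals; (4) all measurements available. Again only (3) applies, with the same limit.

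**Step 2. Apply the rules to an added OAB drug.**

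| Arm | Where added | Breach of a treatment rule? | 9.1 deviation? | Removed by 11.2(3)? |
|---|---|---|---|---|
| CBT | Other hospital | None stated in 0.5 or 5.1 | Yes, (3) | Yes |
| CBT | Study site | None stated | No | No |
| Control | Other hospital | Yes, 0.5 | Yes, (3) | Yes |
| Control | Study site | Yes, 0.5 (and 5.4 if already on a drug) | Not under (3) | No |

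**Step 3. Allow for the rest of section 11.2.** The CBT study-site row does not change: if the participant has all sessions, acceptable intervals and complete data, she meets all four criteria and has broken no stated rule. The control study-site row depends on the reading:
- Criterion (1) taken literally fits no control, so the PPS would contain no controls at all. That cannot be intended.
- With criterion (1) applied to the CBT arm only and the four criteria taken as the definition, the control stays in.
- With the introductory description of adherence applied as a further test, the control is out for breaching 0.5, while the matching CBT participant stays in.

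**Step 4. Scale, on assumed values.** Section 11.1 plans for a difference of 10, SD 20, two-sided 5% and 80% power. The t-test solution is 63.8, so 64 per arm and 128 in total, as stated. 128 / 0.85 = 150.6, against the 150 stated. That is 75 per arm.

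The documents give neither a rate of drug addition nor a drug effect on the OAB-q. Assume on-site additions in 10–20% of an arm:
- 0.10 × 75 = 7.5
- 0.20 × 75 = 15

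So about 8 to 15 participants per arm would pass criterion (3), and fewer would be in the PPS because criterion (4) also requires complete data.

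The shift left in the PPS contrast is (share in CBT − share in control) × drug effect. With a drug effect of 5 to 10 points:
- equal shares: 0
- net excess 10%, 5 points each: 0.10 × 5 = 0.5 points
- net excess 20%, 10 points each: 0.20 × 10 = 2.0 points

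The shift can go either way, and 2.0 is the edge of the assumed range.

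**The case against.** **The PPS is already limited to adherent patients.** This has force for controls. A control who is given a drug on site has broken 0.5, and the introductory description in 11.2 could be used to exclude her. A reader might infer that the gap is identical in both arms; the documents do not support that, because criterion 11.2(1) and the introductory description both bear on controls. The reading does not help in the CBT arm, where there is no stated rule to breach, and it makes the set asymmetric.

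**The primary result is biased or underpowered.** A reader might infer this, but the documents do not support it. ITT includes all allocated participants however the PPS is defined. With 64 per arm and SD 20 (SE = 20 × √(2/64) = 3.54, 126 df), power is 80.1% at 10 points, 76.0% at 9.5 and 61.2% at 8. The two lower figures need an excess of additions among controls, which 0.5 already forbids, so they would measure breaches of an existing rule. With an excess in the CBT arm and no CBT effect, two-sided rejection would be 5.2% at a 0.5-point shift and 8.7% at 2.0. The rates behind all these figures are assumptions.

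**Study visits invite prescribing.** Section 18 lists 7 office visits for the CBT arm and 4 for controls. However, CBT sessions may be held online, and they are 30-minute sessions that follow a manual. The count shows opportunity only.

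**Leaving the CBT arm free may be deliberate.** This stands. Medication change is a declared secondary outcome, and stopping a drug because CBT works may be part of the effect. Freezing medication in both arms would restrict that outcome, and an exception for clinical need would loosen the flat ban on controls. A common freeze is therefore not recommended.

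**Conclusion.** The point holds as a defect in two stated criteria. As written, 9.1(3) and 11.2(3) pass over OAB treatment added at the study site. In the CBT arm this is clear: no rule is breached and the participant stays in the PPS. In the control arm it breaches 0.5, and whether the participant stays depends on how the rest of 11.2 is read. The PPS analysis therefore does not remove on-site co-treatment and may handle the arms differently.

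The consequence is confined to a sensitivity analysis. The wording leaves the ITT primary analysis unchanged. Unequal drug use could affect that analysis in an open-label trial with a self-reported outcome, but its size and direction are unknown and zero is possible. The 8 to 15 participants per arm and the 0.5 to 2.0 points rest wholly on assumed rates and drug effects. The conclusion also rests on the protocol text alone, since the full treatment manual is not reproduced there. Severity: minor.

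**What to change.** In 9.1(3) and 11.2(3), replace the restriction to other hospitals with: any institution, including the study site. State that both items apply to both arms, and limit them to added OAB treatment so that stopping a drug is not counted. Identify cases from the medication-change outcome that the protocol already specifies.

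Keep the flat rule of no additional treatment for controls in 0.5, and keep the PPS as a sensitivity analysis behind ITT.

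The cost is two wording changes and no new outcome. The downside is a few more post-randomisation exclusions from the PPS, possibly related to symptoms, which is a further reason to keep the PPS in its secondary role.

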349  $21+22+23+24+25+26+27+28+29+30+31+32+33)]/125 * 100$   
350

351 Secondary outcomes:  
352 - OAB-q subscales other than HRQoL total scores (2)  
353 The subscales other than the HRQoL total score are calculated as follows.  
354 - Symptom bother:  $[(\text{Question score } 1+2+3+4+4+5+6+7+8)-8]/40 * 100$   
355 - Coping behaviors:  $[48 -(\text{question score } 9+11+16+21+22+26+32+33)]/40 * 100$   
356 - Concern/worry:  $[42 -(\text{question score } 12+13+14+19+23+25+29)]/35 * 100$   
357 - Sleep:  $[30 -(\text{question score } 10+15+17+24+30)]/25 * 100$   
358 - Social interaction:  $[30 -(\text{question score } 18+20+27+28+31)]/25 * 100$   
359 - Overactive bladder symptom score (OABSS)(1)  
360 This is a self-administered questionnaire symptom score for OAB developed in Japan  
361 and used for diagnosis and severity assessment. Regarding severity, a total score of 5 or  
362 less is judged as mild, 6-11 as moderate, and 12 or more as severe.  
363 - King Health Questionnaire (KHQ) (3)

364 A QoL self-administered questionnaire specific to urinary incontinence, consisting of 19  
 365 questions in 8 domains, which has also been validated for OAB.  
 366 - General health perception:  $[(Q1 \text{ score} - 1)/4 * 100]$   
 367 - Incontinence impact:  $[(Q2 \text{ score} - 1)/3 * 100]$   
 368 - Role limitations:  $[(Q3a+Q3b \text{ score} - 2)/6 * 100]$   
 369 - Physical limitations:  $[(Q4a+Q4b \text{ score} - 2)/6 * 100]$   
 370 - Social limitations:  $[(Q4c+Q4d+Q5c \text{ score} - 3)/9 * 100]$  when  $1 \leq Q5c$   
 371 When  $Q5c = 0$ ,  $[(Q4c+Q4d+Q5c \text{ score} - 2)/6 * 100]$   
 372 - Personal relationships: when  $2 \leq Q5a+Q5b$ ,  $[(Q5a+Q5b \text{ score} - 2)/6 * 100]$   
 373 When  $Q5a+Q5b = 1$ ,  $[(Q5a+Q5b \text{ score} - 1)/3 * 100]$   
 374 When  $Q5a+Q5b = 0$ , treat as missing values  
 375 - Emotions:  $[(\text{score of } Q6a+Q6b+Q6c - 3)/9 * 100]$   
 376 - Sleep/energy:  $[(Q7a+ Q7b \text{ score} - 2)/6 * 100]$   
 377 - Severity measures:  $[(Q8a+ Q8b+ Q8c+ Q8d+ Q8e \text{ score} - 5)/15 * 100]$   
 378 - Patient Global Impression-Improvement (PGI-I) (4)  
 379 A multi-item option to evaluate the general improvement score of symptoms using a  
 380 7-point Likert scale self-administered questionnaire, with 1 to 2 defined as improvement,  
 381 and a binary variable of with improvement and without improvement.  
 382 - Patient Global Impression-Severity (PGI-S) (4)  

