 383 It is a multiple-choice instrument that evaluates the overall improvement score of  
 384 symptoms using a 4-point Likert scale self-administered questionnaire. 1 to 2 is defined  
 385 as improvement, and is evaluated with and without improvement as a binary variable.  
 386 - EQ-5D-5L (5)  
 387 A 5-question scale measuring HRQoL with a self-administered questionnaire.  
 388 - Hospital Anxiety and Depression Scale (HADS) (6)  
 389 A 14-item self-administered questionnaire developed to assess anxiety and depression in  
 390 participants with physical symptoms. Anxiety and depression are calculated by  
 391 summing the scores from a point distribution table. Scores of 0-7 indicate no anxiety or  
 392 depression, scores of 8-10 are suspicious diagnoses, and scores of 11 or higher are  
 393 confirmed diagnoses.  
 394 - Frequency voiding chart (FVC)  
 395 The following information is entered in a self-administered form: waking time, sleeping  
 396 time, time of urination, amount of urination per time, frequency of urination, and  
 397 presence or absence of urinary incontinence with a sense of urgency. Of these, the  
 398 average number of urination, urinary incontinence, and urinary urgency frequency per  
 399 24 hours will be used as the evaluation items.

400 - Patient Satisfaction

401 A general improvement score of symptoms was used as a multiple choice to be

402 evaluated using a self-administered questionnaire with a 5-point Likert scale. 1 to 2 is

403 defined as satisfaction with treatment and is evaluated with a binary variable of satisfied

404 or not satisfied.

405 - Change in medication (change, addition, or discontinuation)

406 - Treatment compliance

407 The degree of compliance with the techniques used in each session is evaluated.

|     |           |                               |
|-----|-----------|-------------------------------|
| 408 | Session 1 | Self-monitoring               |
| 409 |           | Improvement of lifestyle      |
| 410 |           | Pelvic floor muscle exercises |
| 411 | Session 2 | Self-Monitoring               |
| 412 |           | Lifestyle modification        |
| 413 |           | Pelvic floor muscle exercises |
| 414 |           | Exposure                      |
| 415 | Session 3 | Self-Monitoring               |
| 416 |           | Improvement of lifestyle      |
| 417 |           | Pelvic floor muscle exercises |
| 418 |           | Exposure                      |

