| 419 | Session 4 | Self-Monitoring               |
| 420 |           | Improvement of lifestyle      |
| 421 |           | Pelvic floor muscle exercises |
| 422 |           | Exposure                      |

423 At the time of evaluation after the end of the intervention, the degree to which each

424 technique is performed (compliance) will be assessed.

425 - Dropout rate

426 The percentage of assigned participants who drop out during the study will be

427 calculated. There will be two types of dropouts in this study: intervention

428 discontinuation and evaluation discontinuation (see "9. Discontinuation Criteria" for

429 details).

430

431 6.3. Measurement methods

432 OAB-q, OABSS, KHQ, GIS, EQ-5D-5L, HADS, FVC, and treatment compliance

433 before the start of CBT, at Week 5 (after treatment ends), Week 9 (4 weeks after

434 treatment ends), and Week 13 (at the end of follow-up) of the paper or online-based

435 registration system (REDCap\*) Patients will be asked to complete a self-administered

436 questionnaire. Dropout rates and incidence of AEs will be confirmed by the therapist at  
437 each visit. Treatment feedback will be completed at the end of follow-up, either on  
438 paper or in a self-administered questionnaire in REDCap\*. The same will be done for  
439 the study at all sites, and data will be collected online with security assured.

440

441 \* REDCap is a data collection and management system developed by Vanderbilt  
442 University in the U.S. under the NIH Clinical Bridging Research Support Grant and  
443 distributed free of charge mainly to academia, and is used at 3090 facilities in 128  
444 countries around the world. In Japan, Osaka City University provides the system; on  
445 April 1, 2017, the Department of Clinical Statistics, Graduate School of Medicine,  
446 Kyoto University contracted with Osaka City University to begin research use of the  
447 system. Under this contract, the data server is dedicated to Kyoto University, which is  
448 contracted by Osaka City University, and its management is entrusted to Osaka City  
449 University. The data server is equipped with complex security measures. Access to the  
450 server and system is restricted by user accounts and passwords issued to individuals,  
451 and all audit trails are recorded.

452

453

454 **The schedule of this study.**

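### Section 6.2 counts a PGI-S severity score of 1 to 2 at a visit as improvement, although that score describes a state and not a change

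*Protocol*

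**What the plan says.** Section 6.2 names the instrument "Patient Global Impression-Severity (PGI-S) (4"), so by the protocol's own name it rates severity. The description under that name says otherwise: "It is a multiple-choice instrument that evaluates the overall improvement score of" symptoms. The responder rule follows: "symptoms using a 4-point Likert scale self-administered questionnaire. 1 to 2 is defined", continuing "as improvement, and is evaluated with and without improvement as a binary variable". The rule uses the score at a visit and does not mention baseline.

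The entry directly above, for the Patient Global Impression-Improvement (PGI-I), has the same cut on a different scale: "7-point Likert scale self-administered questionnaire, with 1 to 2 defined as improvement".

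Section 6.3 gives the measurement times. The list "OAB-q, OABSS, KHQ, GIS, EQ-5D-5L, HADS, FVC, and treatment compliance" is collected "before the start of CBT, at Week 5 (after treatment ends), Week 9 (4 weeks after" treatment ends) and week 13. I read GIS as the two global impression scales. The schedule table independently marks the secondary outcomes at time point 0, so a baseline PGI-S is planned.

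Section 4.2 sets severity at entry by the OABSS alone. Nothing there excludes a woman who rates herself 1 or 2 on the PGI-S at baseline. No other section gives a change-based definition of PGI-S improvement or prints the labels of its four levels.

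**The concern.** The PGI-I asks about change, so a cut on its score at one visit can define improvement. The PGI-S, going by its name, asks how bad things are now. A cut on that score says where a woman stands at the visit and nothing about where she started. Followed as written, the rule can call a woman improved when she has not changed or has got worse. It can deny improvement to a woman who has moved out of the worst category. It can even label a woman improved at the assessment before CBT begins.

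At stake is what the trial may report from this endpoint. A published PGI-S improvement rate for each arm would be read as the share of women who got better, and it would stand beside a PGI-I improvement rate that sounds the same but measures something else.

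**Working it through.** The plan gives no figure to reproduce here, so the check enumerates every possible case.

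**Inputs.** Four levels, 1 to 4, and a rule that counts a follow-up score of 1 or 2 as improvement (both section 6.2). A baseline score is scheduled (section 6.3 and the schedule table). Assumption: a higher score means more severe, because the protocol does not print the labels.

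**Comparison.** Let b be the baseline score and w the follow-up score. The protocol's rule is w ≤ 2. Actual improvement is w < b. There are 4 × 4 = 16 pairs.

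| Baseline b | w = 1 | w = 2 | w = 3 | w = 4 |
|---|---|---|---|---|
| 1 | wrong: unchanged, counted as improved | wrong: worse, counted as improved | agrees | agrees |
| 2 | agrees | wrong: unchanged, counted as improved | agrees | agrees |
| 3 | agrees | agrees | agrees | agrees |
| 4 | agrees | agrees | wrong: better, counted as not improved | agrees |

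- Counted as improved without improving: 3 pairs (1 to 1, 2 to 2, 1 to 2).
- Counted as not improved despite improving: 1 pair (4 to 3).
- Total misclassified: 3 + 1 = 4 of 16; the other 12 agree.
- Of the 6 one-level moves (1 to 2, 2 to 1, 2 to 3, 3 to 2, 3 to 4, 4 to 3), 2 are wrong: 1 to 2 and 4 to 3.
- Of the 4 no-change states, 2 are wrong: 1 to 1 and 2 to 2.

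**Opposite direction.** If 1 were the most severe level, actual improvement would be w > b.

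- The rule would be positive for the 8 pairs with w of 1 or 2. Only 1 to 2 among them is an improvement, so 8 − 1 = 7 are wrong.
- There are 6 improving pairs in all, so the rule would miss 6 − 1 = 5.
- That gives 7 + 5 = 12 of 16 misclassified. The rule would be naming the two most severe levels improvement.

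**Effect on a reported rate.** Let p be the share of an arm at level 1 or 2 at baseline. If nobody in the arm changes, the reported improvement rate is p, whereas the true rate is 0. The protocol does not give p; for an assumed 10%, 25% or 40% the reported rate is 10%, 25% or 40%. This restates the assumption and does not estimate the error. Entry requires moderate or severe OAB by OABSS, which may make low baseline ratings uncommon.

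**The case against.** The best defence is that this is a wrong label and not an invalid comparison. Allocation is randomised 1:1, so women already at level 1 or 2 at baseline are expected equally in both arms. The share at 1 to 2 at a visit is a legitimate attained-state endpoint. That stands. A reader might infer that already-mild women inflate the control rate in particular and so bias the difference between arms. The protocol does not support that: the same share enters both arms in expectation.

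A second argument is that section 11.3.2 applies the primary method to the secondary outcomes, and that method models change from baseline with baseline as a covariate. This does not repair the definition. Section 6.2 has already made the PGI-S a yes/no variable based on the visit score, and how a change-from-baseline model would apply to it is not explained.

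Third, the wording looks carried over from a neighbouring entry; similar improvement wording also appears under Patient Satisfaction. That is a plausible cause, but the text still fixes a definition that would be followed as written.

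Fourth, missing a move from 4 to 3 is a feature of any attained-state cut. That is fair, and it is no fault once the endpoint is called a state. It is a fault while the endpoint is called improvement.

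Finally, the reach is limited: the PGI-S is one of 13 secondary outcomes listed in section 0.6.

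**Conclusion.** The concern holds as an error in the definition. Section 6.2 describes a severity rating as an improvement score and counts a score of 1 to 2 at a visit as improvement, and nothing elsewhere in the protocol corrects it.

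If higher means more severe, 4 of the 16 possible score pairs are misclassified, including 2 of the 6 one-level moves. If the scale runs the other way, the rule labels the most severe states as improvement. The conclusion therefore does not depend on the direction, although the specific examples do.

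The counts are of possible score pairs. A reader might take them as the share of women misclassified, but the protocol gives no PGI-S distribution from which to derive that share.

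The per-arm improvement rates would be misreported. The between-arm comparison remains valid as a comparison of a severity state. The primary outcome, the sample size and the hierarchical testing in section 11.3.1 are not affected. The point should be corrected, but it does not threaten the trial's main conclusion.

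**What to change.** In section 6.2, describe the PGI-S as a rating of severity, print the labels of its four levels, and choose one of two routes:

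- **(a) Measure change.** Define improvement as a move of at least one category towards lower severity from the participant's own baseline PGI-S, or analyse the four-level score adjusted for baseline.
- **(b) Keep the cut.** Report the share scoring 1 to 2 as a severity state at the visit, named from the printed labels, and do not call it improvement.

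Keep the rule that 1 to 2 means improvement for the PGI-I only.

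The cost is a few sentences. On the reading of GIS given above, the baseline PGI-S is already scheduled, so no new data are needed; section 6.3 could name the PGI-S explicitly to remove doubt. The drawback of the responder definition under (a) is that women already at the lowest severity level at baseline can never be counted as improved. Their number should be reported by arm if that definition is chosen.
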